**Risks**

The anticipated risks and discomfort associated with research procedures are not greater than those that would be ordinarily encountered during routine clinical care or psychological assessment. Additionally, many Veterans who participate in research of this nature report positive experiences. However, there is potential risk that the subject matter of the study assessments may cause participants to feel uncomfortable or upset. Consequently, the voluntary nature of the survey will be emphasized during recruitment and informed consent. Additionally, although we are not targeting a high-risk population for recruitment in this study (i.e., there is no inclusion criteria regarding suicidal ideation/attempt), resources (e.g., Veterans Crisis Line; information on how to access emergency care; the PI’s phone number) will be provided to all Veterans in the consent form and online platform, in case participants wish to speak to someone about their participation in the research study or about VA resources; these safeguards will help to mitigate this potential risk.

Participants randomized to SHUTi may experience increased tiredness due to restricted time in bed (this is part of the behavioral treatment for insomnia). To minimize the risk associated with sleep restriction, the SHUTi platform does not recommend participants restrict sleep fewer than five hours. The initial assigned sleep window is also comparable to how much total sleep the participant gets (based on individualized sleep diary data), but the sleep time is restricted to a smaller window. For example, rather than allowing a participant to get 6 hours of sleep while spending 8 hours in bed, a participant will be asked to spend only 6 hours in bed. To further minimize risks associated with sleep restriction, we will instruct participants that they may contact us if they have significant concerns. Based on the situation, we will provide recommendations, including changing their sleep window or incorporating naps. Participants will also be told to avoid operating a car or other heavy machinery when they feel tired. As needed, we will instruct participants to contact their primary care provider or seek professional help at a sleep clinic.

There is also a potential risk of loss of confidentiality and/or privacy. However, a number of protections will be put in place to maintain the confidentiality of records and reduce risks to privacy (see “Data Security and Storage” section below) and this risk is not greater than what is encountered in everyday life activities that require the physical or digital transmission of information. Furthermore, the web-based platforms used in this study all have industry standard safeguards. Moreover, while there is some risk associated with participating in research and disclosing sensitive information, consenting research participants typically agree that the benefits outweigh risks of this nature, and only those who agree to participate after being informed of the potential risks will be included.

**Benefits**

The primary benefit of this study is generalizable knowledge to help better understand whether SHUTi may be an efficacious cCBT for delivery of CBT-I in a Veteran population. If efficacious, this delivery method may help improve Veteran access to a less expensive and EBT for insomnia. It could potentially reduce health disparities by providing access to an EBT for Veterans that seek care at facilities where CBT-I is not available and for Veterans living in rural areas where access to care and treatment involves significant barriers.

Participants randomized to the educational website control and SHUTi may receive the following benefits: knowledge about the diagnosis and symptoms of insomnia, its etiology, methods of monitoring sleep, and general treatment strategies. Participants randomized to SHUTi will receive an interactive intervention that may lead to the reduction of insomnia and comorbid symptoms.

**Safety Monitoring**

Based on the topic of this study, it is not believed that participating in the study places participants at increased risk. However, some participants may be at risk for suicidal ideation due to factors beyond the study and participants will be asked about several suicide risk factors during assessments. There are no clinical cutoffs for the Adult Suicidal Ideation Questionnaire that indicate definite or imminent risk for suicide and no total score is associated with an indication for immediate treatment. During the consent process, all participants will be informed that study team members will not be actively monitoring assessment responses and that immediate clinical needs should be addressed by calling the Veteran’s Crisis Line or 911. The Veterans Crisis Line contact information will be embedded in the web-based platforms as a resource for Veterans who may need additional support, regardless of their score on any specific assessment. From a scientific perspective, it is also important to not provide active outreach/resources to some participants (based on potential total scores) as this could influence the nature of the intervention being provided and could interfere with our ability to determine whether or not the interventions delivered (SHUTi or Educational Website Control) were associated with decreases in suicide risk (Exploratory Objective 1.4). Notably, there is no evidence to suggest that asking about suicidal ideation increases risk for suicide.

***Data Security & Storage***

B*e*Health Solutions/Pear Therapeutics, the companies that will be hosting the study platforms, employs a secure browsing connection that includes SSL certificates that are Transport Layer Security (TLS) 1.2 utilizing strong key exchange (ECDHE_RSA with P-256) and strong cipher (AES_128_GCM) components. In terms of encrypted storage, B*e*Health Solutions/Pear Therapeutics AWS EBS drives are encrypted with industry standard AES-256 algorithms. Furthermore, B*e*Health Solutions/Pear Therapeutics employs a high-level architecture to separate identifying and non-identifying data: one private server is configured behind a firewall where secured data resides; only individuals with approved access onsite are able to connect access this server; a second server is utilized to maintain the front-end Web system so that participants offsite can access the system. Data submitted by participants are captured and then transferred to the private secure server. Participants only need a user ID, password, and email to register and receive study reminder emails. Despite the many industry-approved standards noted above and the high-level architecture of B*e*Health Solutions/Pear Therapeutics’ platform, study-related information (i.e., responses to assessments) cannot be completely guaranteed. This risk will be thoroughly outlined during the consent process.

Minimizing risks pertaining to data security will be achieved by employing safeguards built into the framework of the VA Office of Research and Development (R&D). The PI and data manager will consult with the ECHCS VA Privacy Officer and Information Security Officer through VA (R&D) on data security matters. All data captured within the web-based portals will be transferred to the VA. All data received will be stored within the VA firewall. The data can only be retrieved from within the VA network and will be user restricted so that only members of the research team can access the data. This data will not be kept on laptops that do not meet the VA standards for encryption, anti-virus protection, and firewall security. Data will not leave the VA network except as a deidentified aggregate datasets.

A data use agreement (DUA) with the study sponsor will be utilized to oversee all data sharing that is required by the study sponsor.

Procedures designed to maintain confidentiality will include formal training sessions for all study personnel in the importance of confidentiality and procedures to be followed, as well as formal mechanisms for limiting access to all information that can link data to individual participants. [name], the VA R&D office, and the VA Privacy Officer will be responsible for working with the project staff to ensure the integrity of adherence to patient confidentiality.

**E. Potential Scientific Problems:**

There is a potential that recruitment of participants will be slower than necessary to reach our

goal of 226 participants randomized. If this is the case, we will submit a protocol amendment to change recruitment strategies and our methodological approach. Attrition may be another potential scientific problem. We have estimated 25% attrition in our study design, which is a conservative estimate given that prior RCTs of SHUTi have reported pre-to post-assessment attrition rates from 0-12%, to help reduce the influence of attrition. To improve retention throughout the trial and maximize data collection at designated assessment time points, we will also request that participants provide us with contact information of family and/or friends who would be privy to changes in participant contact information after informed consent; this strategy has improved retention in previous MIRECC studies. Reminder cards will be utilized during follow-up periods to remind participants about study enrollment and to encourage them to contact us in the periods between assessments if contact information has changed.

***Data Integrity***

[name] will work with others members of the research team to ensure the integrity of the data by overseeing the monitoring of data collection. Monitoring data collection will entail quarterly checks of all participant data. Designated team members will work with the VISN 19 MIRECC Data Core to check data for completeness and accuracy to minimize data collection errors (or to identify “problem areas”).

**F. Data Analysis Plan:**

***Sample Size***

Power was based off of the nine outcomes comprising Specific Aim 1, Hypothesis 1.1. Given these nine outcomes (insomnia symptom severity based on the ISI, physical and mental component summary scores on the Veteran’s SF-36), a Bonferroni correction was used and we assume an alpha level of 0.0167. We additionally assume a two-sided test of hypothesis and used the two-sample t-test procedure in PASS v13.0.11 to calculate power. Using any pair power, and the Horn sequential procedure121-122 to control the familywise error rate, with a final sample of at least 170 completing the post-intervention assessment (85 per group), we have 80% power to detect an effect size of 0.6 (medium effect size) for each outcome. As we assume an attrition rate of 25%, 226 participants will be randomized to achieve at least 85 per group completing the post-intervention assessment.

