***Analysis Plan***

All analyses will assume a two-sided test of hypothesis and a significance level of 0.05, unless otherwise noted. Preliminary descriptive and graphical analyses (e.g., boxplots, scatterplots) will be used for data checking and visualization. Demographic and clinical characteristics (including but not limited to age, gender, PTSD, BDI-II scores, BAI scores, and the Life Experiences Survey for the six-month and one-year outcomes) will be compared between groups using t-tests, chi-square tests, Wilcoxon rank-sum tests or Fisher’s exact tests as appropriate to check randomization. Any variable that is found to be different between the groups at the p<0.10 level, and is a plausible potential confounder in consideration of the association under investigation, will be included as a covariate in the analyses described below. This includes an examination as to whether suicide risk variables will be included as covariates.

Given that the aim of the RCT is to test the efficacy of SHUTi, we will perform a per-protocol analysis such that those participants who do not have post-intervention data will not be included in the analysis. Additionally, we will perform a sensitivity analysis using the last value carried forward for those who drop out. This conservative contrast will give some insight into the effectiveness of the intervention and bolster the efficacy findings if they are consistent with the primary analysis.

Primary Aim, Hypothesis 1.1. The primary analyses will be the comparison between groups of the change in 1) insomnia symptom severity as measured by the ISI, 2) physical health as measured by the physical component of the Veteran’s SF-36, and 3) mental health as measured by the mental component summary score on the Veteran’s SF-36, from Time 1 to Time 2. Statistical inference regarding the difference between intervention groups will be based on the estimated coefficient for a group indicator variable in each of three analysis of covariance models with the change from Time 1 to Time 2 for each outcome serving as the dependent variable. Additional covariates will include the baseline value of the outcome to improve precision of the estimate, and any potential confounders discovered in the randomization check. To control for the three primary comparisons, the significance level will be set to 0.0167.

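### The sample-size paragraph counts nine outcomes but corrects for three, and its stated inputs give 93% power for an effect of 0.6 on each outcome, not 80%

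*Protocol*

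**What the plan says.** The Sample Size paragraph (protocol, section IV.F) opens with "Power was based off of the nine outcomes comprising Specific Aim 1, Hypothesis 1.1". The parenthesis that follows names three: "insomnia symptom severity based on the ISI, physical and mental component summary scores on the" Veteran's SF-36. On the significance level it says "a Bonferroni correction was used and we assume an alpha level of 0.0167". On the method it says "We additionally assume a two-sided test of hypothesis and used the two-sample t-test procedure" in PASS. It then adds "Using any pair power, and the Horn sequential procedure" as the means of controlling the familywise error rate, "with a final sample of at least 170 completing the post-intervention assessment (85 per group"), and concludes that "we have 80% power to detect an effect size of 0.6 (medium effect size) for each outcome".

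The Analysis Plan for Hypothesis 1.1 specifies three analysis of covariance models, one for each of the same three outcomes, and says: "To control for the three primary comparisons, the significance level will be set to 0.0167".

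**The concern.** Two things in one paragraph do not agree.

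- **The count.** Nine outcomes are claimed, three are named, and the correction is for three.
- **The power.** Every input needed to check the 80% is printed, and 80% does not follow from them.

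This paragraph is where the protocol derives the 226 participants to be randomised. As written, it does not tell a reader whether the calculation covered three tests or nine, whether the detectable effect is 0.5 or 0.6, or whether the 80% refers to each outcome, to at least one, or to all of them.

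**Working it through.** **Inputs, all from the Sample Size paragraph:** two-sided two-sample t-test; n = 85 per group, so df = 2 × 85 − 2 = 168; alpha = 0.0167; standardised difference d = 0.6; stated power 80% for each outcome.

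**Step 1: the correction.** 0.05/3 = 0.0167. 0.05/9 = 0.0056. The printed level is a three-test correction.

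**Step 2: the plan's own figure.** Power is the probability that a noncentral t variable with 168 df and noncentrality d × √(n/2) exceeds the critical value. The opposite tail is negligible.

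- Noncentrality: 0.6 × √(85/2) = 0.6 × 6.519 = 3.91.
- Critical t for two-sided 0.0167 on 168 df: 2.417.
- Power: **93.1%** (93.6% by the normal approximation).

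The stated 80% is not reproduced. The gap of 13 points is far more than rounding or the choice of approximation can explain.

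**Step 3: the effect that does have 80% power.** At d = 0.50 the noncentrality is 0.50 × 6.519 = 3.26 and power is 79.9%. Solving for exactly 80% gives d = 0.50. Conversely, 60 per group would be enough for d = 0.6 at 80% power.

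**Step 4: nine tests taken literally.** At alpha = 0.0056 the critical t is 2.809. Power at d = 0.6 is 86.3%, the effect with 80% power is 0.56, and 75 per group would be enough for 0.6.

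**Step 5: the other stated conditions.** I read any-pair power as the chance that at least one outcome is significant. The protocol gives no correlation between outcomes, so a range is needed.

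| Reading at d = 0.6, 85 per group | Power |
| --- | --- |
| Any of three, independent: 1 − (1 − 0.931)³ | >99.9% |
| Any of three, correlation 0.8 (simulation) | about 98% |
| Any of nine, correlation 0 to 0.8 | about 97% or more |

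A step-down procedure is never less powerful than plain Bonferroni. Both conditions therefore move the figure away from 80%.

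**Step 6: readings that do come near 80%.**

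| Reading | Power | Printed words it contradicts |
| --- | --- | --- |
| d = 0.5, each outcome, alpha 0.0167 | 79.9% | the effect size of 0.6 |
| All three significant at fixed 0.0167, independent: 0.931³ | 81% | each outcome; any-pair power |
| All nine significant, Holm-type step-down | 78% independent, 81% at correlation 0.3 | each outcome; any-pair power; alpha 0.0167 |

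Treating the named sequential procedure as a Holm-type step-down is my assumption.

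**Step 7: attrition.** 226 × 0.75 = 169.5, which agrees with 170 completers to within rounding. The number randomised is not in question.

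**The case against.** The strongest reply is that nothing in the trial changes. The error is conservative: power for 0.6 on each outcome exceeds 80% with three tests (93%) or nine (86%). The Analysis Plan fixes the confirmatory analysis clearly, with three outcomes, three models and a level of 0.0167, so only the sample-size narrative is unclear. All of this stands, and it makes the point a reporting correction.

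A second reply is that the software run may have been sound and only its description wrong. That also stands as a possibility. The document cannot show which of the readings near 80% was used, or whether any was. A reader might infer that the authors must have computed the chance of all three outcomes being significant, since 0.931³ is 81%. The protocol does not support that: it is one of three readings near 80%, it needs independent outcomes and a fixed 0.0167, and under a Holm-type step-down the same joint power is about 92%.

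A reader might also infer that a null result would be misjudged as beyond the trial's reach. Nothing in the protocol says that effects of 0.5 will be treated that way, and a completed trial is read from its confidence intervals.

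None of this makes the printed statement true. The paragraph contradicts itself on the count, and its power figure does not follow from its own inputs.

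**Conclusion.** The point holds as an error in the sample-size statement that should be fixed. With the printed inputs, power at 0.6 is 93% per outcome against 80% stated, and the effect with 80% power is about 0.50 against 0.6 stated. With nine tests the corresponding figures are 86% and 0.56. These per-outcome results rest only on the printed inputs and the usual t-test assumptions. The any-outcome and all-outcome figures also depend on the correlation between outcomes and on the testing procedure.

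The trial is not underpowered for 0.6, and no change to the sample size follows. Nor does it follow that the trial is too large: 60 per group would suffice for 0.6, but 85 is what an effect of 0.50 requires at close to 80% power, and the protocol does not show which effect the sponsor meant to target.

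**What to change.** 1. Check the original software run for the number of tests, the effect size, the definition of power and the multiplicity procedure.
2. Change the count from nine outcomes to three, to match the Analysis Plan.
3. Replace the power sentence with: *With 85 completers per group and two-sided alpha 0.0167, power is 80% for a standardised difference of 0.50 and 93% for 0.60 on each outcome.*
4. Remove the any-pair power and the sequential procedure, or reconcile them with the fixed 0.0167 in the Analysis Plan. If a joint power is reported, name the procedure and the assumed correlation.
5. If the run shows that nine tests were meant, state alpha 0.0056 and 80% power for 0.56, and change the Analysis Plan to match.

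Keep 226 randomised. The cost is one reworded paragraph, plus a matching edit to the Analysis Plan only if nine tests were intended.

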***Analysis Plan***

All analyses will assume a two-sided test of hypothesis and a significance level of 0.05, unless otherwise noted. Preliminary descriptive and graphical analyses (e.g., boxplots, scatterplots) will be used for data checking and visualization. Demographic and clinical characteristics (including but not limited to age, gender, PTSD, BDI-II scores, BAI scores, and the Life Experiences Survey for the six-month and one-year outcomes) will be compared between groups using t-tests, chi-square tests, Wilcoxon rank-sum tests or Fisher’s exact tests as appropriate to check randomization. Any variable that is found to be different between the groups at the p<0.10 level, and is a plausible potential confounder in consideration of the association under investigation, will be included as a covariate in the analyses described below. This includes an examination as to whether suicide risk variables will be included as covariates.

Given that the aim of the RCT is to test the efficacy of SHUTi, we will perform a per-protocol analysis such that those participants who do not have post-intervention data will not be included in the analysis. Additionally, we will perform a sensitivity analysis using the last value carried forward for those who drop out. This conservative contrast will give some insight into the effectiveness of the intervention and bolster the efficacy findings if they are consistent with the primary analysis.

Primary Aim, Hypothesis 1.1. The primary analyses will be the comparison between groups of the change in 1) insomnia symptom severity as measured by the ISI, 2) physical health as measured by the physical component of the Veteran’s SF-36, and 3) mental health as measured by the mental component summary score on the Veteran’s SF-36, from Time 1 to Time 2. Statistical inference regarding the difference between intervention groups will be based on the estimated coefficient for a group indicator variable in each of three analysis of covariance models with the change from Time 1 to Time 2 for each outcome serving as the dependent variable. Additional covariates will include the baseline value of the outcome to improve precision of the estimate, and any potential confounders discovered in the randomization check. To control for the three primary comparisons, the significance level will be set to 0.0167.

Hypothesis 1.2 and 1.3. A similar analysis will be performed for the above noted outcomes on the change from Time 1 to Time 3 and to Time 4 to determine persistence of group differences to six months and one year post intervention. Additionally, a sensitivity analysis will be performed utilizing a mixed-effects model and all available data, with estimation of the change from Time 1 to Times 2, 3 and 4. The sensitivity analysis will be evaluated for each hypothesis and if it is not consistent than the results for the specific hypothesis will be considered inconclusive.

Exploratory Objective 1.4. For the exploratory outcomes of sleep diary variables (sleep efficiency, sleep onset latency, and wake after sleep onset), risk for SDV (ASIQ), anxiety (BAI), depression (BDI-II), PTSD symptoms (PCL-5), the methods outlined above for the primary analyses will be utilized for the change from Time 1 to Time 2, Time 3, and Time 4.

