*Life Experiences Survey (LES):* Based upon the Holmes-Rahe Life Change Index Scale [67], the LES queries participants about a variety of life events (e.g., death of a close friend, loss of child). Participants will be asked to indicate yes or no as to whether any of these life events have occurred since the last study assessment as a way to characterize major life events that may be associated with long-term changes in sleep patterns.

*Military Suicide Research Consortium (MSRC) Common Data Elements (CDE).* The MSRC CDE is a composite measure of several items taken from commonly utilized self-report assessments. The CDE are required to be administered to all participants by the funding agency.

*Military Suicide Research Consortium (MSRC) Demographics:* Required by the funding agency, this demographics form will collect information (e.g., gender, race, education, military history) to describe key demographic and military participant characteristics.

*Morningness/Eveningness Questionnaire (MEQ)* [68]: The MEQ is a 19-item self-report instrument designed to assess an individual’s chronotype: evening, intermediate, or morning. Information about participant chronotype will help determine whether certain chronotypes may be more or less sensitive to conventional insomnia treatment.

*Posttraumatic Stress Disorder Checklist for DSM-5 (PCL-5)* [69]. The PCL-5 is a psychometrically sound self-report measure that assesses the severity of PTSD symptoms in the past month.

*Sleep Diary* [70]. A Sleep Diary includes assessment of 10 standard sleep parameters: time to fall asleep; number and length of awakenings at night; time of awakening and arising from bed in the morning; length of naps; subjective sense of how refreshed the participant felt upon awakening as well as how sound they sleep during the night; and amount of medication and alcohol used as a sleep aid. Data suggest that sleep diary assessments are a valid and reliable way to collect information on sleep parameters. They have also been found to provide a more comprehensive understanding of sleep patterns than can be achieved using objective measures of sleep, such as polysomnography, which is typically administered for one to two nights only [71]. Sleep diaries will provide information on over the counter and prescribed sleep medication use.

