| Internet Impact and Effectiveness Questionnaire | 10** | Feedback on perceptions of SHUTi’s effectiveness |
| MSRC Common Data Elements | 40 | Study sponsor measure – abbreviated self-report items |
| **6-Month Follow-Up Post-Intervention Assessment (Time 3): 95-100 minutes** | | |
| Insomnia Severity Index (ISI) | 5 | Assess insomnia symptoms |
| Veteran’s SF-36 | 15 | Assess health-related quality of life |
| Adult Suicidal Ideation Questionnaire (ASIQ) | 10 | Assess past-month suicidal ideation |
| PCL-5 | 5 | Assess PTSD symptoms |
| Beck Depression Inventory-II (BDI-II) | 5 | Assess depressive symptoms |
| Beck Anxiety Inventory (BAI) | 5 | Assess anxiety symptoms |
| Follow-Up Questions – SHUTi | 5** | Feedback on experiences and perceptions of SHUTi |
| Follow-Up Questions – Sleep and Demographics | 5 | Information on changes in sleep medication/treatment and demographics |
| Life Experiences Survey | 5 | Information on life changes since last assessment |
| MSRC Common Data Elements | 40 | Study sponsor measure – abbreviated self-report items |
| **1-Year Follow-Up Post-Intervention Assessment (Time 4): 95-100 minutes** | | |
| Insomnia Severity Index (ISI) | 5 | Assess insomnia symptoms |
| Veteran’s SF-36 | 15 | Assess health-related quality of life |
| Adult Suicidal Ideation Questionnaire (ASIQ) | 10 | Assess past-month suicidal ideation |
| PCL-5 | 5 | Assess PTSD symptoms |
| Beck Depression Inventory-II (BDI-II) | 5 | Assess depressive symptoms |
| Beck Anxiety Inventory (BAI) | 5 | Assess anxiety symptoms |
| Follow-Up Questions – SHUTi | 5** | Feedback on experiences and perceptions of SHUTi |
| Follow-Up Questions – Sleep and Demographics | 5 | Information on changes in sleep medication/treatment and demographics |
| Life Experiences Survey | 5 | Information on life changes since last assessment |
| MSRC Common Data Elements | 40 | Study sponsor measure – abbreviated self-report items |

*Assessment administered only to participants randomized to SHUTi that did not complete all 6 cores. **Assessments administered only to participants randomized to SHUTi.

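### The Life Experiences Survey is collected only after randomisation, so it cannot check randomisation and should not be a candidate covariate in the six-month and one-year models

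*Protocol*

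**What the plan says.** **Timing of the survey.** In section IV.A of the protocol (Additional Measures), participants report "whether any of these life events have occurred since the last study assessment". Table S1 lists the survey under Time 3 (six months) and Time 4 (one year) only, with the purpose "Information on life changes since last assessment". It does not appear under Time 1 or Time 2. Under Random Allocation and Concealment, allocation follows completion of the Time 1 assessment.

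**Use of the survey.** The Analysis Plan in section IV.F names it among the characteristics to be compared: "and the Life Experiences Survey for the six-month and one-year outcomes) will be compared between groups". The purpose of the comparison stands at the end of its list of tests: "Wilcoxon rank-sum tests or Fisher’s exact tests as appropriate to check randomization". The selection rule follows: "Any variable that is found to be different between the groups at the p<0.10 level, and is a plausible potential confounder" for the association being studied, "will be included as a covariate in the analyses described below".

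**Where it would enter.** The Hypothesis 1.1 models take the baseline value of the outcome and "any potential confounders discovered in the randomization check". Hypotheses 1.2 and 1.3 reuse this form: "A similar analysis will be performed for the above noted outcomes on the change from Time 1 to Time 3 and to Time 4". The exploratory outcomes use the same methods at Times 2, 3 and 4.

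**The concern.** A randomisation check looks at what the arms were like when they were allocated. A variable first measured about six months after the intervention cannot do that. If the arms differ on it, the cause is chance, an effect of treatment on the events or on how they are reported, or a difference in who was followed up. None of these is a fault of the allocation.

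Nor can such a variable confound the comparison, because it cannot have influenced assignment. It can lie on the path from treatment to outcome, in which case adjustment takes out part of the effect. It can also share an unmeasured cause with the outcome, in which case adjustment opens a biased path once treatment affects the variable. The p<0.10 rule selects it most often when treatment has shifted it, which is when adjustment does harm.

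At stake are Hypotheses 1.2 and 1.3, which carry the trial's claims about durability, and the exploratory analyses at Times 3 and 4.

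**Working it through.** **1. Is the survey's absence at Times 1 and 2 a slip in the table?** The minutes in Table S1 answer this.
- Time 1: 5+15+5+10+5+5+5+10+40 = 100, the stated total, without the survey.
- Time 2: common measures 5+15+10+5+5+5+40 = 85; with the SHUTi-only items 5+15+5+10 = 35 more, 120. This is the stated 85 to 120, without the survey.
- Time 3, and likewise Time 4: common measures including the survey 5+15+10+5+5+5+5+5+40 = 95; with the SHUTi-only item 100. This is the stated 95 to 100.

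The table is consistent with itself: the survey belongs to Times 3 and 4 only, after allocation.

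**2. Does the covariate rule reach it?** Yes. It is named in the comparison, the rule covers any variable compared, and the Time 3 and Time 4 models copy the Time 2 model. The Time 2 model is not reached: the survey has not been given by then, and the plan ties it to the later outcomes.

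**3. Illustrative size.** The protocol gives no figure for this. It defines no survey score, standard deviation, relation to the outcomes, or expected number at Times 3 and 4. Everything here is therefore assumed: a score in SD units, a slope b of outcome on score of 0.2 to 0.4 SD per SD, and 85 per arm, which the Sample Size section gives for completion at Time 2.
- Trigger: 1.645 × sqrt(2/85) = 0.252 SD. At an assumed 60 to 70 per arm it is 1.645 × sqrt(2/60) = 0.30 to 1.645 × sqrt(2/70) = 0.28 SD.
- Shift in the estimate = arm difference × b: 0.25 × 0.2 = 0.05 to 0.25 × 0.4 = 0.10 SD. At 60 to 70 per arm it is 0.28 × 0.2 = 0.056 to 0.30 × 0.4 = 0.12 SD.

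**4. When is the shift a bias?** In 3,000 simulated trials per setting (85 per arm, assumed true total effect −0.60 SD, b = 0.4), the averages were:

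| Effect of treatment on survey (SD) | Survey admitted at p<0.10 | Estimate if always adjusted | Estimate under the rule |
|---|---|---|---|
| 0 | 10% | −0.60 | −0.60 |
| −0.2 | 37% | −0.52 | −0.55 |
| −0.3 | 62% | −0.48 | −0.50 |
| −0.5 | 94% | −0.41 | −0.41 |
| +0.3 | 62% | −0.72 | −0.70 |

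The unadjusted estimate averaged about −0.60 throughout. The third row agrees with theory: −0.60 + 0.3 × 0.4 = −0.48.

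In a further setting the survey had no effect on the outcome, but an unmeasured cause had a loading of 0.5 on each. With a treatment effect of −0.3 SD on the survey, the adjusted estimate averaged −0.53; theory gives −0.60 + 0.3 × 0.5 × 0.5 = −0.525.

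So there is no average bias if treatment leaves the survey alone. Otherwise there is bias, and its direction follows the sign of the treatment's effect on the survey.

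**The case against.** Several points against a stronger reading stand.

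- **The primary result is not exposed.** A reader might infer that the main comparison is compromised. It is not: it runs from Time 1 to Time 2, before the survey is given.
- **Adjustment is conditional.** It needs p<0.10 and a judgement that the variable is a plausible confounder. A careful analyst could reject a consequence of treatment on the second condition. This protects only in part: the survey is named expressly for these outcomes, and section IV.A says it is collected because such events may go with long-term changes in sleep.
- **Life events may be largely beyond treatment's reach.** The only examples in section IV.A are the death of a friend and the loss of a child, which an insomnia website would hardly alter. Adjustment would then merely correct a chance imbalance, with no average bias. But the protocol speaks of a variety of events, self-reported in the same assessment as the outcomes, so an effect on reporting cannot be ruled out.
- **The size is not grounded in the protocol.** A reader might set 0.05 to 0.10 SD against the design effect of 0.6 and conclude that 8 to 17% of the effect is lost (0.05/0.6 and 0.10/0.6). The documents do not support this. The 0.6 and the 85 per arm belong to Time 2, the slope is assumed, and the shift is the size of an adjustment, which is bias only if treatment caused the difference. That the treatment effect would be removed altogether is likewise unsupported.

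No passage makes the survey a valid randomisation check, and that part of the point is unanswered.

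**Conclusion.** The plan is wrong as written, within limits. A variable that exists only after randomisation is put into the randomisation check and made eligible as a covariate for the Time 3 and Time 4 contrasts. That it cannot check randomisation or confound the comparison follows from the protocol's own timing and needs no assumption.

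That adjustment would bias the results is conditional. The survey must meet both parts of the rule, and treatment must affect the events or their reporting. The bias could then go either way, so the rule cannot be defended as conservative. The shift of 0.05 to 0.10 SD is an illustration on assumed inputs, not an estimate for this trial.

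This should be fixed, but it does not threaten the primary analysis.

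**What to change.** In the Analysis Plan, delete the Life Experiences Survey from the variables compared to check randomisation and from the candidate covariates. State that covariates in every efficacy model are limited to variables measured before randomisation. That boundary is better than Time 1 alone, because the baseline sleep diaries are completed in the two weeks before the Time 1 assessment and are needed as baseline values for the diary outcomes. It also makes clear that the other listed scores, which are repeated at later visits, enter at their baseline values.

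Report the survey by arm at Times 3 and 4 descriptively. If its relation to sleep is of interest, examine it in a separate analysis labelled exploratory.

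The cost is a sentence or so of text. Data collection, sample size and significance levels do not change. The amendment should be made before anyone sees Time 3 or Time 4 data by arm, so that the covariate choice cannot depend on differences seen after treatment.
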